### Ethics

This trial will be conducted in compliance with the Declaration of Helsinki (1964 and amendments), Good Clinical Practices (GCP) and all relevant local laws and regulations. Patients will give their written informed consent prior to the start of any study-related procedure and the study protocol has been approved by the reference Ethics Committee of each participating site (Additional file 1: Appendix).

## Discussion

The aim of the LIAISON study is to estimate the level of asthma control and quality of life in a European real-life setting and their evolution during 1 year, using validated self-administered tools such as the six-item ACQ and Mini-AQLQ. Further objectives are: to evaluate the reasons for lack of asthma control, the medication adherence, the impact of pharmacological treatment, the number of severe exacerbations and healthcare resources use.

Several real-life asthma studies have been reported elsewhere but the variability in patients’ samples due to current treatments, the geographical location and the criteria for exclusion from study participation has led to different outcomes in terms of prevalence of asthma control. Moreover, it is difficult to compare the results of these studies due to the different methods used in data collection, which included patient self- or web-administered questionnaires, office-based or hospital-based physician consultations [18].

With the inclusion of more than 8,000 patients in the cross-sectional phase and of more than 4,000 in the longitudinal phase of the study, the LIAISON study will be the largest naturalistic study ever performed in 12 European countries to investigate asthma control and the impact of asthma control on quality of life and future risk of exacerbations. Furthermore, the longitudinal phase of the study will provide important information on the adequacy and effects of management strategies implemented in each country to reach control in the following year.

Previous multinational studies carried out in Europe have shown important differences among countries in the level of asthma control. Rates of not well-controlled asthma ranged from 65% in Germany to 40% in Spain [16] or from 63% in Italy to 41% in France [17]. Among ICS users, the prevalence of uncontrolled asthma ranged from 20% in Iceland to 67% in Italy [12]. Differences in symptoms’ control between Western and Central/Eastern Europe, with somewhat better outcomes in Western countries, were also reported [6]. In most of these studies, assessments were performed by phone- or mail-transmitted questionnaires based on patient perception of asthma control and severity of symptoms [6,12,20], or were internet-based with data obtained from the European National Health and Wellness Survey [16,17]. Moreover, all the above studies were cross-sectional and, therefore, gave no information on the prospective monitoring of patients with poor asthma control.

In the LIAISON study, the assessments will be performed during patient visits at the clinics, thus allowing a real-life asthma management approach based on disease monitoring. It has been suggested that monitoring outcomes and taking appropriate action through regular visits may improve current levels of asthma control. Behavioural factors such as smoking and non-adherence may reduce the efficacy of treatment and patient perceptions influence these behaviours. Under-treatment may also be related to patient underestimation of the significance of symptoms, and lack of awareness of achievable control [14].

We chose the 6-item ACQ for the evaluation of asthma control because it is applicable to all adults with asthma, is considered reliable and reproducible. It has been fully validated for use in both clinical practice and clinical trials, and the minimum clinically important difference has been established [13]. The ACQ also has strong discriminative properties, i.e. it is able to detect small differences between patients with different levels of asthma control and it is very sensitive to within-patient changes in asthma control over time [27]. The overall population included in the LIAISON study will be representative of the European real-life setting. A sample size of at least 400 patients enrolled in at least eight centres in each country will also allow reliable country-specific analyses of data collected in a number of sites that are representative of the entire National territory in all involved countries [6]. Previous reports have included a limited number of sites [12] or a smaller number of patients in some countries than in others [6], while other studies have been performed in sites with non-homogeneous distribution in the same country [21].

Asthmatic smokers and pregnant women, who are usually excluded from randomised controlled trials (RCT) in asthma, will be included in the LIAISON study in order to obtain a large sample that is as representative as possible for the real-life asthmatic population in Europe. Smoking is a critical factor associated with increased risks of not achieving control, excess mortality, asthma attacks and exacerbations [22,29]. Within all obstructive respiratory disorders, asthmatics who smoke represent a substantial portion that increases with age [30]. Therefore, the non-exclusion of smokers in previous observational studies [16,18] may in part explain the increased frequency of poor asthma control in these studies compared to rates observed in RCT, and may have led to differences among countries. One weakness of this study is the requirement for questionnaire completion and patient consent, which will tend to bias the data towards those managed in good clinical settings. On the other hand, the recruitment of consulting patients could tend to bias towards those who are uncontrolled. Other important endpoints of the study will be the description of the reasons for poor control (from both the patient’s and investigator’s perspectives), the evaluation of patient adherence to antiasthmatic therapy and the impact of suboptimal asthma control on healthcare costs. There are limited data available on the cost-effectiveness of treatment strategies aimed at different levels of asthma control [31,32] and other local studies investigating cost-effectiveness of asthma treatment strategies driven by different target levels of asthma control are ongoing [33].

To our knowledge, the LIAISON study will be the first to include both a cross-sectional and a longitudinal phase to assess asthma control and quality of life in a large population from a number of European countries. Therefore, the study will allow obtaining pan-European data while evaluating among-country differences in care with consistency and its impact from an economic perspective on the different national healthcare systems.

In conclusion, it is expected that the multinational LIASON study will provide novel data on the level of asthma control and quality of life in clinical practice in Europe. The results of the study will contribute to understanding the reasons for poor asthma control and to evaluate the proportion of patients with uncontrolled or partly controlled asthma who achieve asthma control in a 1-year observation period. Moreover, the study will provide data on adherence to treatment, number of exacerbations and healthcare resource use, together with insights into the impact of pharmacological treatment on both clinical and pharmacoeconomic outcomes.

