The primary objectives of the prospective phase (which will include only patients with uncontrolled and partly controlled asthma classified according to the six-item ACQ score) are to evaluate the proportions of uncontrolled/partly controlled patients reaching asthma control after 12 months from the cross-sectional phase visit, to assess the health-related quality of life and the factors associated with gain of asthma control as well as predictors of those who are at future risk of exacerbations.

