## Methods/design

### Study design

Figure 1 shows the design of the cross-sectional phase and the prospective phase of the study. Subjects satisfying entry criteria will be evaluated in the cross-sectional phase of the study. Asthmatic patients with uncontrolled/partly controlled asthma will be followed for the 12-month prospective phase. Follow-up visits will take place approximately 3, 6 and 12 months after the cross-sectional phase visit.

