### Study population

The study population will include approximately 8,150 patients attending about 160 outpatient hospitals or General Practice clinics distributed across 12 European countries (Austria, Belgium, France, Germany, Greece, Hungary, Italy, the Netherlands, Poland, Spain, Turkey and the United Kingdom). At least 400 patients in about eight centres will be enrolled in each participating country. Consecutive patients visiting the centre during the estimated 12-month recruitment period will be enrolled.

Male and female adult (aged ≥18 years) patients with a clinical diagnosis of asthma (according to GINA guidelines and confirmed by a chest physician) for at least 6 months, and receiving the same antiasthmatic drugs in the last 4 weeks before enrolment, will be eligible for study participation after signing the informed consent.

Patients participating in a clinical trial within the previous 4 weeks or patients suffering from conditions and illnesses that might interfere with the study purpose, according to the investigator’s evaluation, will be excluded from the study.

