#### Six-item asthma control questionnaire (ACQ)

The six-item ACQ [13] includes a measure of the top five asthma symptoms (woken at night by symptoms, day-time symptoms, limitation of daily activities, shortness of breath and wheeze) and the use of quick-relief bronchodilators. The asthma control level will be evaluated according to the following thresholds: controlled asthma: ACQ score ≤ 0.75; partly controlled asthma: 0.75 < ACQ score <1.5; uncontrolled asthma: ACQ score ≥ 1.5.

As long as many factors are to be considered when a symptom-based approach is being used to achieve optimal disease control [22]*,* the possible reasons for poor control (e.g. comorbidities, seasonal worsening, depression, etc.) will be collected both according to the doctors’ and patients’ opinions using a multiple choice system from a drop down list.

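### Follow-up is selected on one ACQ above 0.75 and judged by the same cut-off, so part of the gain of control would occur with no change in care and cannot be read as an effect of management strategies

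*Protocol article*

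**What the plan says.** Under Study population, recruits are clinic attenders: "Consecutive patients visiting the centre during the estimated 12-month recruitment period will be enrolled". Under Objectives, entry to the prospective phase depends on a single questionnaire score: it is the phase "which will include only patients with uncontrolled and partly controlled asthma classified according to the six-item ACQ score". Study design repeats the rule: "Asthmatic patients with uncontrolled/partly controlled asthma will be followed for the 12-month prospective phase". The ACQ section sets the threshold, "controlled asthma: ACQ score ≤ 0.75".

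Table 1 uses the same threshold for the outcome. Its primary longitudinal objectives include the proportions controlled, partly controlled and uncontrolled at 12 months, and the proportion switching to controlled. Under Statistical analysis, all outcomes are stratified by country, models include confounders if the exploratory analysis identifies them, and mean score changes are taken from the cross-sectional visit, which is the visit that selected the patients.

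The Discussion then says that the longitudinal phase will provide "important information on the adequacy and effects of management strategies implemented in each country to reach control". It also describes the study's aim as estimating control and quality of life in a European real-life setting and how they evolve over one year. Among the weaknesses it concedes that "the recruitment of consulting patients could tend to bias towards those who are uncontrolled". It does not mention that such patients may drift back towards their usual level.

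**The concern.** ACQ varies within a patient from visit to visit. Patients chosen because one reading was above 0.75 include some whose usual level is lower, and on re-measurement some fall to 0.75 or below with nothing changed in their care. Patients controlled at entry who drift the other way are not followed, so the matching movement out of control is not seen. No second baseline reading or comparison group is described that would allow this component to be separated out.

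Two readings of the results are at stake. A high month-12 proportion could be taken as evidence that management works. A country with more borderline patients at entry could look as if it manages asthma better. An unseen analysis plan could not settle the first point, because the patients needed to estimate the component are not followed.

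**Working it through.** **The plan's own figures (Sample size).** These reproduce.
- Not controlled at entry: 8,150 × (1 − 0.375) = 5,093.75, stated as 5,094.
- Evaluable at month 12: 5,093.75 × 0.80 = 4,075, as stated.
- Half-width for 45%: 1.96 × √(0.45 × 0.55 / 4,075) = 0.0153, stated as ±1.5%.

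**Inputs to the check.**
- 37.5% controlled at entry (Sample size).
- 35.5% partly controlled and 27.0% uncontrolled (the Dutch ACQ study described in Background). With 37.5% these sum to 100%.
- Cut-offs 0.75 and 1.5 (ACQ section).
- Between-visit correlation ρ: not in the documents, so assumed and varied.

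**Model.** Scores at the two visits are bivariate normal with the same distribution at each, so there is no true change.
- a = Φ⁻¹(0.375) = −0.319 and b = Φ⁻¹(0.73) = 0.613.
- SD = (1.5 − 0.75)/(b − a) = 0.75/0.931 = 0.805; mean = 0.75 + 0.319 × 0.805 = 1.007.

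**Formulas.** Φ₂ is the bivariate normal distribution function.
- Apparent gain, all followed = [0.375 − Φ₂(a,a;ρ)]/0.625
- Apparent gain, partly controlled = [Φ₂(a,b;ρ) − Φ₂(a,a;ρ)]/0.355
- Apparent gain, uncontrolled = [0.375 − Φ₂(a,b;ρ)]/0.27
- Unobserved loss among the controlled = [0.375 − Φ₂(a,a;ρ)]/0.375
- Mean ACQ change = −(1 − ρ) × SD × φ(a)/0.625, where φ(a)/0.625 = 0.607

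Example at ρ = 0.7: Φ₂(a,a) = 0.2550 and Φ₂(a,b) = 0.3570.
- All followed: (0.375 − 0.2550)/0.625 = 19.2%.
- Partly controlled: (0.3570 − 0.2550)/0.355 = 28.7%.
- Uncontrolled: (0.375 − 0.3570)/0.27 = 6.7%.

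| Assumed ρ | Apparent gain | As a fraction of 45% | Unobserved loss among controlled | Mean ACQ change |
|---|---|---|---|---|
| 0.95 | 7.7% | 17% | 13% | −0.02 |
| 0.9 | 10.9% | 24% | 18% | −0.05 |
| 0.8 | 15.6% | 35% | 26% | −0.10 |
| 0.7 | 19.2% | 43% | 32% | −0.15 |
| 0.5 | 25.2% | 56% | 42% | −0.24 |

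The proportions depend only on the 37.5/35.5/27 split and ρ on the normal scale. The mean change also uses the fitted SD.

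**Effect of baseline mix at ρ = 0.7.** A 70/30 split of partly controlled to uncontrolled gives 0.7 × 28.7 + 0.3 × 6.7 = 22.1%. A 40/60 split gives 0.4 × 28.7 + 0.6 × 6.7 = 15.5%. Both mixes are illustrations with identical care.

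**Sensitivity to the consulting visit.** Suppose the entry visit is transiently worse by an assumed 0.2 to 0.3 SD. With d for that shift, apparent gain is [Φ(a+d) − Φ₂(a,a+d;ρ)]/0.625. This gives 18–23% at ρ = 0.9, 27–31% at 0.7 and 33–37% at 0.5.

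**The case against.** The strongest defence is that the primary longitudinal objectives are descriptive. A patient who fluctuates into control is controlled at month 12, so the proportion is right as a description, and ±1.5% is its correct sampling precision. That stands. The attribution sits in one Discussion sentence, not in the objectives, sample size or analysis. That also stands, and it limits the point to what the results are said to show.

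The mix effect is moderate. Moving the partly controlled share from 46% to 66% at ρ = 0.7 shifts the rate only from 16.8% to 21.2%. A country with the minimum 400 patients has about 400 × 0.625 × 0.8 = 200 evaluable, a half-width of about 6.9 points. But the shift is systematic, so a larger sample does not reduce it.

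The models may already adjust for confounders, and an analysis plan not shown may name baseline ACQ. Its absence from the article is therefore not counted as an omission.

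A reader might go further than the documents allow:
- *That regression to the mean produces most of the gain.* This depends on a correlation that is not given. The source of the 45% is also not available, so the comparison with 45% shows scale and does not decompose it.
- *That change is seen in one direction only.* Table 1 also reports the uncontrolled share at 12 months, so worsening from partly controlled to uncontrolled is visible. Only loss of control among those controlled at entry is unseen.
- *That the visit schedule departs from usual care.* The Discussion says that "monitoring outcomes and taking appropriate action through regular visits may improve current levels of asthma control", but no usual visit frequency is given for comparison.
- *That gain must require a minimum change because "the minimum clinically important difference has been established".* Control is defined by a threshold, so a minimum-change rule would be a different, optional endpoint and not a correction.
- *That the Background's closing statement of purpose credits management.* It speaks of the level of control, its determinants and its changes, and attributes nothing to management.

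**Conclusion.** The point holds as a limit on inference. Selecting on one ACQ reading and reusing its cut-off as the outcome builds in a component of apparent gain that the design cannot separate from any effect of care. Under a no-change bivariate normal model fitted to the article's split, that component is about 8 to 25 percentage points, beside an expected 45, for assumed correlations of 0.95 to 0.5. Mean change from the selecting visit carries the same component. It is larger in partly controlled than in uncontrolled patients (29% versus 7% at 0.7), so crude country results depend on baseline mix.

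The Discussion's statement that the longitudinal phase informs on the effects of management strategies in each country is therefore unsupported. Its reference to one-year evolution can apply only to patients not controlled at entry. No sample-size figure is wrong. The size rests on the assumed correlation and on identical score distributions at both visits.

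**What to change.** 1. **Discussion, claim.** Restate the longitudinal claim as gain of control among patients not controlled at entry, without attributing it to management strategies. Limit the statement about evolution over one year to that group.
2. **Statistical analysis.** Report gain of control separately for patients partly controlled and uncontrolled at entry. Include continuous baseline ACQ in every country or factor comparison of gain of control.
3. **Discussion, weaknesses.** Name regression to the mean beside the existing caveat on consulting patients.

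The baseline scores are already collected, so the cost is a weaker headline claim and a few extra tables. Step 2 reduces the distortion from baseline mix in comparisons but does not remove the component from the overall proportion, so step 1 is needed in any case.
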